### Statistical analysis

The clinical and questionnaire results will be collected in this study. Among these results, results from the participants both seven clinical evaluations and one questionnaire will all be included in the data analysis. SPSS version 20 statistical package (SPSS, Inc., USA) will be used to analyze all data with *p* < 0.05 indicating statistical differences. Data will be analyzed for all participants in an intent-to-treat plan. Continuous data will be expressed as mean ± standard deviation (M ± SD), or median. For between-group comparisons of baseline characteristics, one-way analysis of variance (ANOVA) or Kruskal-Wallis tests will be used for parametric and non-parametric continuous data, respectively. The chi-square test will be used for categorical data.

According to the intention-to-treat principle, a linear mixed model will be used for analyzing the differences between the three interventions group over time on the outcome variables. Missing data will be assumed missing at random and handle by a linear mixed model by using maximum likelihood.

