### Randomization and blinding

Participants who meet the inclusion criteria and do not meet the exclusion criteria will be informed about the purpose and procedures of the study, what it will involve for them, and any risks involved in taking part as well as how to obtain more information about the study, low- and high-load resistance training and sarcopenia. After informed consent is obtained, subjects will be randomized into one of three groups: LRT-BFR, CRT, or control at 1:1:1 ratio. The randomization sequence, stratified by sex and age, will be generated and stored by a statistician who is not participating in the intervention and evaluation of the study, using SPSS version 20 statistical package (SPSS, Inc., USA). The random numbers and grouping assignments will be delivered in an encrypted electronic file to a research staff from another research for keeping this information. The therapists of this study will check the file and perform the intervention according to the grouping assignments. Except for therapists, all other participating staff, including the statistician, outcome assessors, and data managers will be blinded to the group assignment.

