### Sample size

The sample size was calculated with PASS (version 11.0). According to a previous study, lower limb muscle strength is the most relevant outcome to show the efficacy of blood flow restriction. Thus, it was used as the primary outcome for calculating sample size [43, 44]. According to the data used in the study by Brandner et al. [44], the expected mean changes in lower limb muscle strength were approximately 11% for the BFR training group, 16% for high-load resistance training, and 0% for the control group with a pooled standard deviation of 13%. This sets the estimated total sample size at 42 subjects (14 in each group) to meet 80% power and an alpha of 0.05. Considering the frailty of some older people with sarcopenia, up to a 20% dropout rate is expected. Therefore, the sample size is set at 51 subjects (17 in each group).

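### The mixed model is specified by maximum likelihood for 51 people without naming the sex and age strata or the use of baseline; REML and stratum and baseline adjustment should be written in together

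*Protocol article*

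**What the plan says.** Protocol article, Statistical analysis: "a linear mixed model will be used for analyzing the differences between the three interventions group over time on the outcome variables". Missing data are assumed missing at random, and the plan is to "handle by a linear mixed model by using maximum likelihood". The section names no covariates, baseline handling, covariance structure or outcome scale for the model.

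Protocol article, Randomization and blinding: "The randomization sequence, stratified by sex and age". Allocation is 1:1:1; the number of age bands is not given.

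Protocol article, Primary outcomes: the outcome is an estimated knee-extension 1RM in kilograms, measured at 0, 12 and 24 weeks.

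Protocol article, Sample size: expected changes are "approximately 11% for the BFR training group, 16% for high-load resistance training, and 0% for the control group" "with a pooled standard deviation of 13" percent. "This sets the estimated total sample size at 42 subjects (14 in each group") "to meet 80% power and an alpha of 0.05". Then "up to a 20% dropout rate is expected", which leads to 51 (17 per arm).

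**The concern.** Three features of the model matter in a trial of this size.

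- Estimator. Maximum likelihood does not correct variance estimates for the fixed effects fitted. With 51 people at most, and 42 planned as evaluable, that bias is not negligible.
- Strata and baseline. Sex and age were thought important enough to stratify on, yet the model description names neither, nor says how the baseline measurement enters. Randomization within strata pays off in the analysis only if the strata are in the model.
- Scale. Power was planned on percent change, the outcome is defined in kilograms, and nothing connects the two.

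At stake are the validity of the p-values and some precision. The precision matters because the second objective in the Background is pairwise, while the planned 80% is reached for the three-group test and not for LRT-BFR against control.

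**Working it through.** **1. The plan's own figure.** Inputs from Sample size: means 11, 16 and 0, SD 13, alpha 0.05. One-way ANOVA with noncentrality n·Σ(μ−μ̄)²/SD²: the overall mean is 9 and the squared deviations are 4 + 49 + 81 = 134. At n = 14, 14 × 134/169 = 11.1 and power is 0.826; at n = 13 power is 0.793. So 14 per arm (42) is the smallest size reaching 80%. Then 42 × 1.2 = 50.4, rounded up to 51. Both figures reproduce. For LRT-BFR versus control alone (two-sided t-test, 26 df), the noncentrality is 11/(13·√(2/14)) = 2.24 and power is 0.58.

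**2. Maximum likelihood alone.** With complete data and three arm means, ML divides the residual sum of squares by N and REML by N − 3, so the ratio of standard errors is √((N−3)/N).

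- N = 51: √(48/51) = 0.970, or 3.0% too small.
- N = 42: √(39/42) = 0.964, or 3.6% too small.

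Actual type I error at nominal 0.05:

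| Reference | N = 51 | N = 42 |
|---|---|---|
| Single contrast, t on N df | 0.057 | 0.059 |
| Three-group test, F on 2 and N df | 0.060 | 0.062 |
| Single contrast, normal | 0.063 | 0.066 |

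**3. Strata left out.** Let R² be the share of variance of the analysed contrast explained by sex and age; the protocol does not give it. With balanced strata, the standard error reported without them is 1/√(1−R²) times the correct one: 1.03, 1.05, 1.20 and 1.41 at assumed R² of 5%, 10%, 30% and 50%. This is conservative, the opposite direction to step 2. At N = 51 the two cancel when 1 − R² = 48/51, that is R² = 5.9%. A 20,000-run simulation of one between-arm contrast (complete data, four strata assumed) gave type I error for unadjusted ML at N = 51 (t reference) of 0.055, 0.044, 0.024 and 0.006 at R² of 0, 10%, 30% and 50%.

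**4. Strata added.** In the same simulation at N = 51, ML with strata gave 0.063–0.070 and REML with strata 0.047–0.052. More fixed effects make the ML bias larger: the divisor should now be N − 6 and ML still uses N.

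**5. Baseline.** Assume equal variances σ² at baseline and week 12 with correlation r. A change-score contrast has per-person variance 2σ²(1−r); with a common baseline mean it is σ²(1−r²). The ratio is (1−r²)/(2(1−r)) = (1+r)/2. Taking 13 as the SD of change, with 14 per arm and a difference of 11:

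| Assumed r | Variance ratio | Effective SD | Power, LRT-BFR vs control |
|---|---|---|---|
| change score | 1 | 13.0 | 58% |
| 0.5 | 0.75 | 11.3 | 70% |
| 0.7 | 0.85 | 12.0 | 65% |
| 0.8 | 0.90 | 12.3 | 62% |

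**6. Scale.** The protocol gives no mean or SD in kilograms, so power in kilograms cannot be calculated from it.

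**The case against.** The strongest reply is that much of this is silence. The article gives the model two sentences, and a full protocol or analysis plan may name covariates, baseline handling and scale. That stands against two readings a reader might draw: that the model ignores the strata, and that it works on kilograms. The text neither includes nor excludes sex and age, and it does not say whether kilograms, change, percent change or logs are modelled. Recording in kilograms and planning in percent is not a contradiction, because one can be derived from the other.

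A reader might also infer that the trial's p-values are too small overall. The document does not support that: it is true of ML taken alone, and omitted prognostic strata offset it once they explain about 6% of the variance. Nor is a precision loss from the strata shown. In a group-by-time comparison that includes baseline, constant sex and age effects cancel from within-person change, so the loss depends on how well they predict change. But where they predict change poorly, the offset is also small and the ML inflation remains.

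Finally, the ML wording sits in the missing-data sentence and may only mean likelihood-based handling. That is possible, but it is the only estimator the protocol names, and REML is equally valid under missing at random.

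**Conclusion.** The point holds in a limited form. ML is written into the plan for 51 people and, alone, raises type I error from 0.05 to about 0.057–0.062 with a t or F reference (up to 0.066 for a single contrast with a normal reference). This is modest and rests on a complete-data approximation, not on a full three-visit model with dropout. The net error of the analysis as described is unknown, because the strata's effect on change is not given. Changing only one element is not safe, since strata with ML is more anti-conservative than ML alone.

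The baseline gain, from 58% to 62–70%, depends on the assumed r of 0.5–0.8, on equal variances, and on a change-score contrast as comparator. No size can be put on a power loss in kilograms without assuming kilogram means and variability. A log scale is a reasonable choice, and its absence is not a demonstrated error. The stated sample size figures stand.

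**What to change.** In Statistical analysis, replace maximum likelihood with REML and Satterthwaite degrees of freedom. Name sex and age stratum, as used in the randomization, as fixed effects. Either constrain the arms to a common baseline mean or adjust for baseline. State that the primary outcome is analysed on a relative scale that matches the sample size, for example log 1RM reported as percent change, or else restate the power in kilograms with the mean and SD used.

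The cost is wording only, as sex, age and baseline strength are already collected. The downside is a few degrees of freedom for the added terms and REML standard errors about 3–4% wider than those from ML, which is the correction intended.

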### Safety monitoring

The training intervention will be carried out under the supervision of researchers and trainers. The adverse events (AEs) and serious adverse events (SAEs) will be recorded for all participants during each training session. SAEs will be reported to the sponsor and principal investigator to find a reasonable solution. If necessary, medical services should be provided as compensation to those who suffer harm from trial participation. Subjects have the right to withdraw their consent to participate in the study at any time for any reason, without any consequences for further treatment.

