**Fig. 1 Fig1:**
[figure not shown]
The experimental flow chart showing the patient recruitment, intervention and assessment process

**Table 1 Tab1:** Schedule of enrolment, interventions, and assessments

Period	Screening	Allocation	Intervention period		Close-out	Follow-up
Time point	0 week	0 week	0 week	1–12 weeks	13 weeks	24 weeks
Inclusion and exclusion criteria	X					
Demographic data	X					
Informed consent	X					
Allocation		X				
LRT-BFR group				X		
CRT group				X		
Control group				X		
Body composition			X		X	X
Muscle strength			X		X	X
Muscle performance			X		X	X
Pulmonary function			X		X	X
Blood biomarkers			X		X	X
CVD risk factors			X		X	X
SF-36			X		X	X
Nutritional intake			X	X	X	X
Patient compliance				X	X	X
Dropout reasons				X	X	X
Adverse events				X	X	X

*CVD* Cardiovascular disease, *SF-36* 36-item Short-Form Health Survey, *LRT-BFR* Low-load resistance training with blood flow restriction, *CRT* Conventional high-load resistance training

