### Interventions

#### Group protocols

Before the group protocols begin, all subjects will complete a one-repetition maximum (1RM) strength test to assess their muscle strength and to determine the intensity for resistance training in training groups. In addition, they will complete three pre-intervention lessons with the resistance training exercises to familiarize themselves with the training sessions. Subjects randomized to the control group will receive health education sessions only. The researchers will record the attendance of each participant in each training session. And if a participant misses a scheduled training session, the session will be completed within the training week.

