#### Resistance training program

Both resistance training intervention groups will receive three weekly resistance training sessions for 12 weeks with training intensities specific to their group assignment (see Table 2). Both groups will use Thera-band elastic bands to deliver the resistance exercises. Both groups will perform upper limb exercises (elbow extension and elbow flexion), followed by lower limb exercises (leg press and knee extension). The resistance training protocol of LRT-BFR will consist of 3 sets of 30-15-15 repetitions of each exercise, performed at an increased intensity from 20 to 30% 1RM by different Thera-band elastic bands. Subjects will have a 20-s rest interval between sets and a 30-s rest interval between exercises. The CRT group will perform 3 sets of 15 repetitions at 60% 1RM in the first 4 weeks, 3 sets of 12 repetitions at 65% 1RM in the second 4 weeks, and 3 sets of 10 repetitions at 70% 1RM in the third 4 weeks. They will have a 60-s rest interval between sets. The progressive resistance is also achieved by using Thera-band elastic bands with different tensions.

**Table 2 Tab2:** Details of the training protocol in the intervention groups

Weeks	Group	Sets	Repetitions	Intensity (%1RM)	Frequency (times/week)	Exercises	Interval between sets (s)
1–4	LRT-BFR	3	30, 15, 15	20	3	Elbow extension, elbow flexion, leg press, knee extension	30
	CRT	3	15	60	3		60
5–8	LRT-BFR	3	30, 15, 15	25	3	Elbow extension, elbow flexion, leg press, knee extension	30
	CRT	3	12	65	3		60
8–12	LRT-BFR	3	30, 15, 15	30	3	Elbow extension, elbow flexion, leg press, knee extension	30
	CRT	3	10	70	3		60

*LRT-BFR* Low-load resistance training with blood flow restriction, *CRT* Conventional high-load resistance training

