#### Control group education sessions

The control group will meet once a week at the community center and receive a 60-min educational session on aging and health (see Table 3). Subjects will be instructed to maintain their usual lifestyles, and while some subjects may engage in some form of physical activity, they will not be provided an exercise program nor will they be encouraged to participate in a physical activity involving resistance training. To assess the subject’s usual physical activity levels, the Chinese version of the short form of the International Physical Activity Questionnaire (IPAQ) will be administered every week. The seven items in the short IPAQ provide an assessment of the duration and frequency of walking and moderate- and vigorous-intensity physical activity per week. The short IPAQ is scored by multiplying the duration in minutes per day, frequency in days per week, and a MET value of each activity (walking 3.3 METS, moderate-intensity 4.0 METS, vigorous-intensity 8.0 METS) to create MET-minute scores. The MET-minute scores are summed across activities to create a total MET-minute per week score for walking and moderate- and vigorous-intensity activities.

**Table 3 Tab3:** Details of education session topic in the control group

Week	Group	Education session topic	Frequency (times/week)
1–4	CG	Geriatric diseases and disease risk reduction	1
5–8	CG	Nutrition and physical activity for older people	1
9–12	CG	The importance of social support and care from friends, families, and communities	1

*CG* Control group

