#### Nutritional intake

All the participants will maintain normal dietary habits during the 12-week intervention and follow-up period. They will record all their nutritional intakes including the amount of protein they took by 3-day dietary record (two weekdays and one weekend day in a week) per week on the notebook [30]. The weekly recording work is assisted and supervised by community works.

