### Data management and monitoring

All study information will be stored in Microsoft Excel 365 by a data manager using an electronic database. The database will record all subject data to include the baseline characteristics, pre- and post-assessments, and possible adverse events. The computer and database will use password protection with the database accessible to the study researchers only. To ensure the confidentiality of the data, all subjects will be provided with identification numbers. All researchers will have access to the final trial data. Electronic data and paper documents will be kept for 5 years, after which they will be destroyed. Data Monitoring Committee (DMC), which is independent from the sponsor and competing interests, comprises clinical experts, trial experts, investigators, and a statistician. It will conduct regular monitoring tests to ensure the authenticity of the data.

As for the audition, the project organization will hold a meeting every 6 months to review and evaluate the trial progress. The process will be independent from investigators and the sponsor.

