## Trial status

The study was registered with the Chinese Clinical Trial Register (ChiCTR2100042803) on 28 January 2021. The subject recruiting was started on 1 May 2021. Recruitment is expected to end around June 2021.

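### Adverse events are recorded at training sessions, which the control arm does not have and which stop at week 12, in conflict with Table 1

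*Protocol article*

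**What the plan says.** The Safety monitoring section sets the rule: "The adverse events (AEs) and serious adverse events (SAEs) will be recorded for all participants during each training session". Other parts of the protocol article determine what that rule can deliver.

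- Resistance training program: "Both resistance training intervention groups will receive three weekly resistance training sessions for 12 weeks".
- Group protocols: "Subjects randomized to the control group will receive health education sessions only".
- Control group education sessions, on contact in that arm: "The control group will meet once a week at the community center and receive a 60-min educational session on aging and health".
- Table 1 has a row labelled "Adverse events", marked for weeks 1–12, week 13 and week 24, with no split by arm.
- Objective (2), at the end of the Background, is to compare safety as well as efficacy. As printed, its list of pairs names LRT-BFR against CRT twice and then CRT against the no-strength-training group. The main aim stated just before it also sets both training methods against a non-exercising control.
- Nutritional intake: every participant keeps a dietary record each week, and "The weekly recording work is assisted and supervised by community works".

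**The concern.** The recording rule covers everyone in scope but names an occasion that exists for only two of the three arms. It also names an occasion that has ceased in every arm by the time of the last two adverse-event marks in Table 1. A site that follows the Safety monitoring section and a site that follows Table 1 would collect different data.

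What is at stake is the training-versus-control part of the safety objective. If events are noted three times a week in one arm and rarely or never in another, a difference in counts can arise from the frequency of observation and not from the training. There is a second, smaller route. A participant who stops attending has no further sessions, so a session-based rule stops recording that person. The article lists serious adverse events among its termination criteria, so stopping may be related to harm.

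**Working it through.** The plan gives no figure for adverse-event collection, so there is none to reproduce. The check is a count of scheduled recording occasions, followed by an illustration of what unequal capture could do.

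**Inputs.** Three training sessions a week for 12 weeks (Resistance training program, Table 2). One education meeting a week for 12 weeks (Control group education sessions, Table 3). 17 participants per arm and up to 20% dropout (Sample size).

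**Recording occasions per participant**

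| Reading | LRT-BFR | CRT | Control |
|---|---|---|---|
| Safety monitoring rule as written, weeks 1–12 | 3 × 12 = 36 | 3 × 12 = 36 | 0 |
| Same, with education meetings used for controls | 36 | 36 | 1 × 12 = 12 |
| Safety monitoring rule as written, after week 12 | 0 | 0 | 0 |
| Table 1 marks after week 12 | 2 (weeks 13, 24) | 2 | 2 |

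The three familiarisation lessons that all participants take before the group protocols begin are equal across arms and precede weeks 1–12, so they do not alter the contrast.

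**What unequal capture could do.** Assume the same true risk r of at least one event in every arm, complete capture in the training arms, and capture of a fraction c of the affected controls. The spurious risk difference is r − r·c = r(1 − c). Neither r nor c is in the documents; both are assumptions, so a range is shown. Expected counts are out of 17.

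| r | Training arm | Control, c = 0 | Control, c = 1/3 | Control, c = 1 |
|---|---|---|---|---|
| 10% | 1.7 | 0 (10 points) | 0.6 (6.7 points) | 1.7 (0 points) |
| 20% | 3.4 | 0 (20 points) | 1.1 (13.3 points) | 3.4 (0 points) |
| 30% | 5.1 | 0 (30 points) | 1.7 (20 points) | 5.1 (0 points) |

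The figures in brackets are spurious differences. The column c = 0 is the literal rule, and c = 1 is a weekly enquiry that misses nothing.

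**LRT-BFR versus CRT.** Scheduled occasions are 36 and 36, so the schedule creates no imbalance. At the dropout the plan allows for, 17 × 0.20 = 3.4 participants per arm could leave the session-based record. This contrast is affected only if such stopping differs between the arms or is tied to harm.

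**The case against.** The strongest reply is that the rule should not be read in isolation. It says everyone is covered, Table 1 schedules adverse events in all arms through week 24 along with dropout reasons, and the data management section has the database hold possible adverse events for all participants. Controls are met weekly, complete an activity questionnaire weekly, and keep the same weekly dietary record as everyone else. On that view the intention is plain and only one sentence is loosely worded.

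Much of this stands. It means that zero capture in controls is the literal reading and not a forecast, and that one cannot say that people who stop training are lost to safety observation. It does not remove the conflict: the only sentence that states when events are recorded names an occasion that controls do not have, and no text says how events are collected from controls or from anyone after week 12. This is a stated rule that disagrees with the schedule, so it is not a detail that a condensed article leaves to a fuller document.

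A reader might also infer that harms are reviewed too late, because "the project organization will hold a meeting every 6 months to review and evaluate the trial progress" and "Recruitment is expected to end around June 2021". The documents do not support that. The six-monthly meeting is described as an audit of progress, not a harms review, and the start of its cycle is not given. Counted from the recruitment start on 1 May 2021 it would first meet about 1 November; counted from registration on 28 January 2021 it would meet about 28 July. If the last participant enrols in June, 12 weeks of training end no earlier than 24 August (1 June + 12 weeks), so the July date falls during training. Training is supervised, serious events go to the sponsor and the principal investigator, and a monitoring committee's safety remit may be set out in a fuller document.

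**Conclusion.** The point holds as an internal conflict that puts one stated comparison at risk. Followed as written, the Safety monitoring rule gives 36, 36 and 0 recording occasions in weeks 1–12 (36, 36 and 12 at best) and none afterwards, against Table 1 marks in all arms through week 24. Training-versus-control safety counts are therefore exposed to unequal ascertainment. Under the assumed true risks of 10% to 30%, the spurious difference ranges from 0 up to 10 to 30 points, depending wholly on how much is captured in controls.

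Two stronger conclusions should not be drawn. The first is that the comparison is already biased or that the training arms will show more events: that depends on practice at the site, which the document does not settle. The second is that the 3-to-1 ratio of contacts translates into a similar ratio of events: that would need a detection probability per contact, which the document does not give. LRT-BFR versus CRT, the comparison in the trial's title, has equal scheduled sessions and is touched only through participants who stop attending.

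**What to change.** Reconcile the Safety monitoring section with Table 1 by stating one collection method for all arms:

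- Ask one standard adverse-event and serious-adverse-event question set of every participant, in all three arms, at the weekly dietary-record contact in weeks 1–12, and again at the week 13 and week 24 assessments. Include people who have stopped training.
- Base the between-arm safety comparison on these common enquiries. Scheduled enquiries then number 12, 12 and 12 in weeks 1–12, plus two in each arm afterwards.
- Keep recording events seen at training sessions, but report them separately and for the training arms only.

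The cost is a short question set added to contacts that already exist, and slightly more adverse-event data to process. An answer can reveal the allocation, so the questions are best asked by someone other than the blinded outcome assessor. Sample size and interventions are unchanged.
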